| **Protocol Title:** | Incorporation of a Health Equity Approach to Hospital Violence Intervention Programs: The Integration of a Community and Hospital Based Initiatives to Reduce Gun Violence in a Large Metropolitan Area |
| --- | --- |
| **Principal Investigator:** | [name] and [name] |
| **Co-Investigators:** | Drs [name], [name], [name], [name], [name], [name], [name], and [name] |
| **Study Coordinator:** | [name] |
| **Study Team:** | [name], [name], [name] [name], [name] |
| **Population:** | Males and female patients age 16-35 years who are victims of firearm injury, excluding self-harm, and unintentional injury |
| **Number of Sites:** | Single site – UTHealth/Memorial Hermann Hospital |
| **Clinical Trial:** | Phase III trial \| NCT06263647 |
| **Study Duration:** | 5 years |
| **Subject Duration:** | 12 months |

**General Information**

One of the most significant risk factors for violent injury is having a previous violent injury; thus, it is imperative to intervene with patients in the hospital setting to reduce the risk of reinjury through violence intervention programs. This study develops and implements the Houston Hospital-Based Violence Intervention Program (Houston-HVIP) in Memorial Hermann Hospital-Texas Medical Center. This study will evaluate the effectiveness of the Houston-HVIP in reducing firearm violence and improving recovery among young adults in urban trauma settings, thus ultimately improving community safety.

**Background Information**

Firearm violence is a leading cause of injury and mortality in the United States. ***Victims of firearm violence are often stuck in a cycle of violence, as they are twice as likely to die or be hospitalized from a violent event compared to those without a history of violent victimization***. Therefore, hospital-based intervention programs (HVIPs) can be crucial to provide holistic services and connections to critical community-based violence interventions that support firearm violence victims and reduce reinjury risk. Developing interventions to impact firearm violence requires a transdisciplinary approach with community–city–hospital interventions. The lack of a current HVIP in the greater Houston area–the fourth largest city in the United States–highlights the need to develop and implement this program as a critical community-based intervention to reduce firearm violence. Therefore, the current study aims to create the Houston-Hospital-Based Violence Intervention program at Memorial Hermann Hospital in the Texas Medical Center in Houston, Texas, as a community-level response to firearm violence. In Aim 1, during the UG3 phase, we will develop a coalition of internal and external stakeholders to advise on the formation and oversee the implementation of the Houston-HVIP. We will create the culture prime for the reception of the HVIP by developing an inter-professional, trauma-informed care educational platform. In our second aim, during the UG3 phase, we will implement and evaluate the Houston-HVIP program to determine the effectiveness of reducing repeat violent events by a program participant. The Houston-HVIP will feature a randomized controlled trial, with a high-intensity case management service program (Houston-HVIP) tailored to the firearm victim's needs, and standard of care program with referrals to community-based services. The program is guided by critical stakeholders, including hospital leadership, public health advocates, law enforcement, community and city leaders, and a multidisciplinary team of experts. This intervention will be rigorously evaluated to understand program effectiveness and acceptability, the impact of reinjury on those enrolled in each arm of the program, and the role of social determinants of health on firearm injury to the participant and the community.

**Objectives**

**Our primary aims for the proposed study are:**

**Aim 1: In the UG3 two-year planning period (2023-2025), our primary objective** is to develop a coalition of internal and external stakeholders to advise the formation and oversee the implementation of the Houston-HVIP program. In the planning period, we will create the culture prime for the reception of the HVIP by developing an inter-professional, trauma-informed care educational platform. Finally, we will develop the study evaluation framework, recruitment, retention, and measurement protocols and test the measures through a feasibility test of the intervention in preparation for the UH3 phase.

**Aim 2a: In the UH3 phase (2025-2028)**, we will conduct a randomized controlled trial to evaluate the effectiveness of Houston-HVIP in reducing the occurrence of repeat firearm violent events among children (16 and 17 yr olds) and adults receiving care at Memorial Hermann Hospital in Houston, Texas (*n* = 274); intervention group will receive the Houston-HVIP program, while the comparison group will receive standard of care with referrals to the community-based services.

**Our UH3 secondary aims are:**

**Aim 2b.** To determine the impact of the community-engaged Houston-HVIP program on violent re-injury and mental and behavioral health. We anticipate that those enrolled in the Houston-HVIP will have significantly less violent reinjury as measured by (a) return to the hospital for an intentional firearm and non-firearm injury, (b) self-reported firearm or non-firearm victimization, or (c) mortality from a firearm or non-firearm injury.

**Aim 2c.** To determine the impact of the community-engaged Houston-HVIP program on physical and behavioral health during the 12-month follow up period. We anticipate that compared to standard of care, those enrolled in the Houston-HVIP program will have significantly better health as measured by (a) PTSD [PCL-2], (b) Health and Wellbeing [SF-12], and (c) Aggression [Copeland-Linder].

**Aim 2d.** To identify the predictors of implementation success, including dosage, reach, fidelity, and acceptability from the perspective of gun violence victims, health care providers, and community violence intervention specialists**.** Data from quantitative surveys, and qualitative interviews of key stakeholders will inform an understanding of key features leading to the successful implementation of the HVIP program.

**Impact:** The proposed project brings together a transdisciplinary team to establish the first HVIP in the TMC. If found to be effective, the program has the potential to significantly reduce the incidence of firearm violence in Houston, Texas, and inform violence intervention efforts in other healthcare settings in the city and state. As a part of our study design, we are excited to participate in the Community Level Interventions for Firearm Prevention Research Network through this funding mechanism, thus contributing to the larger community in the advancement of firearm injury research.

**Study Design**

This five-year proposal will consist of a two-year planning period to develop and refine the Houston-HVIP procedures and train staff, thus instilling the culture transformation with a community-based approach and finalizing the recruitment, retention, measurement, and implementation protocols for the intervention delivery. This stage will be followed by three years focused on program implementation, data collection, and overall program evaluation.

**Aim 1: Develop a coalition of internal and external stakeholders to advise the formation and oversee the implementation of the Houston HVIP program.** In the planning period, we will create the culture prime for the reception of HVIPs by developing an inter-professional, trauma-informed care educational platform. Finally, we will develop the study evaluation framework, recruitment, retention, and measurement protocols and test the measures through a feasibility test of the intervention in preparation for the UH3 phase.

Using a community-centered approach, we will engage internal and external stakeholders to form a coalition that advises the implementation of the Houston HVIP. We will recruit members to include hospital leadership, community leaders, trauma specialists, law enforcement officers, city leadership, injury prevention specialists, previous victims of violence, and representatives of the Health Equity Collective to a goal of 15 total members. To convene, leverage and assess the coalition, we will undergo a series of modified intervention mapping steps to outline the scope of the Houston HVIP by focusing on steps 1-3 of Intervention Mapping (IM).^1,2^ The first step of IM requires the advisory board to conduct a thorough needs assessment, propose a logic model, and articulate program goals. Group facilitation techniques such as nominal group and brainstorming will play a crucial role in these meetings by encouraging active participation, open discussion, consensus generation, and problem-solving among group members. We will combine quantitative and qualitative research methods in Step 1. First, we will review the epidemiological analysis of firearm injury data obtained from the Memorial Hermann hospital system to estimate the prevalence and incidence of firearm injuries, specifically with a focus on firearm assault, in Harris County for the advisory board members. We will conduct a comprehensive review of relevant literature to identify the most critical and modifiable factors related to community violence and modifiable factors. The second step of IM is the foundation for our intervention by identifying who and what will change due to our efforts. The product of this step is a set of matrices at different ecological levels, including individual, community, and societal. These matrices will ensure that our intervention is comprehensive and inclusive in its community-based approach. In the last step, the objective is to confirm the scope and sequence of the program, develop a mechanism for feedback to the program leadership, and examine evaluation tools for comprehensiveness.

Led by [name], we will develop an educational series on trauma-informed care to reach the critical health professionals and stakeholders involved in the Houston HVIP development and implementation. As we develop the culture of change, we will implement a series of educational interventions that will be guided by the Kirkpatrick model, an established model of analyzing and evaluating educational programs; we will evaluate the effectiveness of our educational programming at multiple levels. The core levels of the Kirkpatrick model evaluate the learner in their satisfaction of the education (Level 1), change in learning (Level 2), and change in behavior (Level 3) and impact to the population (Level 4).^3,4^ Each assessment of the level of learning will demonstrate the rigor of the educational process and the sustained impact on the learner.

This educational platform will include a series of asynchronous and live educational venues taught by experts in the field to transform the culture at Memorial Hermann Hospital and thus ensure adequate support for the planned intervention. Educational models will be developed by [name], [name], [name], [name], and [name], with core learning objectives of 1) Describing violence and risk factors, 2) Reviewing risk factors for recidivism, and 3) Roles of healthcare and communities to reduce gun violence. [name] will oversee module development to ensure alignment with goals. All educational events will be evaluated via a pre/post-test model (TIC Provider Survey v2.0 - All patient version), with assessments in knowledge, attitude, and behavior around core learning objectives obtained via quantitative surveys utilizing a series of Likert, yes/no, or sliding scaled answers before and immediately post-educational modules. Quantitative analysis will be performed via paired t-test or Chi-squared test, and additional statistical analyses will be used as appropriate.

Within our program, we will focus on identifying victims of firearm violence and presenting them to the Memorial Hermann Hospital at the Texas Medical Center during the study period. We will have two levels of patient support: 1) The Houston-HVIP program (Treatment Intervention) and 2) Standard of care (Comparison Group). Patients will be randomly assigned to either condition, thus supporting the ability to generate causal estimates of each treatment condition of the HVIP program on primary and secondary outcomes.

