**Study Flow**

**Evaluation of UG3 Phase Activities:** Coalition meetings will be conducted in-person and virtually to accommodate all participants, while thorough note-taking ensures no loss of input. Summaries of these meetings are shared with the Community Advisory Board (CAB) members in a timely manner. One or more investigators will lead the groups ([name], [name], [name]). Participants will be compensated $50/meeting for their time. Data captured in the process will be secured on password-protected storage drives at UTHealth for ongoing data management, and Institutional Review Board approval will be obtained. We plan to hold six meetings prior to the pilot phase and at least 2 virtual meetings after the initiation of the pilot group to provide an update to the group.

**Qualitative Analysis:** We will conduct semi-structured virtual interviews with coalition members who volunteer to do the interview. These interviews will be audio-recorded and professionally transcribed. Participant names will be removed during transcription. A multidisciplinary research team will use a four-step approach to analyze qualitative data. First, the team will collectively read the transcripts collected from each interview to better understand the general themes. Through this process, a deductive codebook will be created to allow labeling of the text from the interviews. These codes will be generated in group analysis sessions until the team has agreed on all codes. Second, the team will code all the text. We will group emerging findings into categories of themes using an immersion-crystallization approach, including inductive thematic identification.^5^ Third, transcripts will be read by a second coder, and coding inconsistencies will be discussed and resolved by consensus between the two coders. Fourth, the team will consider how the findings relate to the current health literature, health services research, and intervention development.

**Quantitative Analysis:** Surveys will be conducted with coalition members to assess the feasibility and acceptability of aspects of programming, consisting primarily of Likert ratings. To determine the impact of program design, we will conduct an analysis of variance (ANOVA) based on the portion of the program being evaluated. Other analysis approaches may be incorporated if appropriate.

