
**Statistical Analysis.** Primary analysis will follow the intention-to-treat principle. A Weibull regression model for interval-censored data will be used to compare the risk of firearm violence between the two study groups. A two-sided alpha of 0.05 will be used to determine statistical significance. Since prespecified adjustment of important baseline covariates can provide enhanced power, the regression model will be adjusted for race/ethnicity, biological sex, and age. In addition, we plan to balance-cross case managers across the two arms to protect against potential agent effects, if any, and will adjust case manager as a fixed factor covariate in our analytic model^83^. We will carry out several secondary analyses to gain comprehensive insights and ensure the robustness of findings. Although the random enrollment of participants to the two treatment arms should ensure comparability with respect to known and unknown variables, imbalance may occur by chance. Descriptive statistics for baseline characteristics known or suspected to be associated with outcomes will be prepared for the two randomization groups. Chi-square statistics and Wilcoxon rank sum tests will be used to evaluate baseline differences between the arms for categorical and continuous variables, respectively. Any variables with baseline differences will be adjusted in secondary sensitivity analyses. Next, to assess heterogeneity of the intervention effect, we will examine interactions between the randomization group and important baseline risk factors (e.g., race/ethnicity). The corresponding interaction terms will be added individually into the regression model to examine potential effect modification. Finally, we will carry out a per-protocol analysis as a sensitivity analysis.

The secondary outcomes that are measured longitudinally (e.g., SF-12) will be analyzed using appropriate longitudinal models, such as the (generalized) linear mixed model with a suitable distribution and link function, including group, time (categorical), group by time interaction, as well as subject-specific random effects to account for the repeated measures. We will first conduct a contrast to test the intervention effect across the post-baseline time points. Group-specific means and between-group differences will be estimated at each time point with 95% confidence intervals.

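### The pre/post evaluation of staff education names a chi-squared test without saying it is paired; in its ordinary sense that test loses power on linked yes/no answers

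*Protocol*

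**What the plan says.** The education programme is described in the Protocol under Study Design, Aim 1. The design is stated plainly: "All educational events will be evaluated via a pre/post-test model". Answers are collected "utilizing a series of Likert, yes/no, or sliding scaled answers before and immediately post-educational modules", so some items are yes/no and some are scored. The evaluation model is about change in the learner, including "change in learning (Level 2), and change in behavior (Level 3").

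The analysis is given in one sentence: "Quantitative analysis will be performed via paired t-test or Chi-squared test", followed by a closing clause that allows further analyses. It does not say which test serves which type of item. No paired method for categorical answers, such as McNemar's test, is named anywhere in the Protocol.

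The Statistical Analysis paragraph for the trial shows how the document uses the term elsewhere: "Chi-square statistics and Wilcoxon rank sum tests will be used to evaluate baseline differences between the arms". There it is the ordinary test between two independent groups.

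**The concern.** A pre/post design gives two answers from each learner. The paired t-test respects that for scores. A chi-squared test in its usual form treats the pre answers and the post answers as two separate groups of people, which they are not.

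People who answer yes before a module tend to answer yes after it, so the two answers are usually positively correlated. A test that ignores this uses too large a standard error for the change. The consequence is not false claims of success but real gains on yes/no items that fail to reach significance. What is at stake is how well the education evaluation can show that staff knowledge, attitudes or behaviour shifted.

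**Working it through.** The Protocol gives no sample size, power or alpha for this evaluation, so there is no stated figure to reproduce. The check is of the error rate and power of the two candidate tests.

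**Inputs.** From the Protocol: a pre/post design, yes/no items, and an unqualified chi-squared test. Assumed: a two-sided alpha of 0.05 (the Protocol's "A two-sided alpha of 0.05 will be used to determine statistical significance" is written for the primary trial analysis), the within-person correlation ρ, the number of learners n, and the proportions answering yes.

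**Type I error.** Let the true proportion be p both before and after.

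- True variance of the observed change: 2p(1−p)(1−ρ)/n
- Variance used by the ordinary chi-squared test: 2p(1−p)/n

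The test therefore rejects only when a standard normal variable exceeds 1.96/√(1−ρ) in absolute value, and the actual error is 2[1 − Φ(1.96/√(1−ρ))].

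| ρ (assumed) | 1.96/√(1−ρ) | Actual type I error | Simulated, n=200, p=0.5 |
|---|---|---|---|
| −0.3 | 1.72 | 8.6% | 8.8% |
| 0 | 1.96 | 5.0% | 5.1% |
| 0.2 | 2.19 | 2.8% | 2.9% |
| 0.3 | 2.34 | 1.9% | 2.0% |
| 0.5 | 2.77 | 0.6% | 0.6% |
| 0.7 | 3.58 | 0.03% | 0.04% |

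In the same simulations McNemar's test (no continuity correction) stayed between 5.0% and 5.2%.

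**Power, assumed n=150, change from 60% to 70%.** At ρ=0.5:

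- √(0.6×0.4×0.7×0.3) = 0.2245, so the share answering yes both times is 0.42 + 0.5×0.2245 = 0.5322.
- Changers: yes to no 0.6 − 0.5322 = 0.0678; no to yes 0.7 − 0.5322 = 0.1678; together 0.2355 before rounding.
- True standard error of the change: √[(0.24 + 0.21 − 2×0.5×0.2245)/150] = 0.0388.
- Null standard error, chi-squared: √(2×0.65×0.35/150) = 0.0551. Power ≈ Φ[(0.10 − 1.96×0.0551)/0.0388] = Φ(−0.21) ≈ 42%.
- Null standard error, McNemar: √(0.2355/150) = 0.0396. Power ≈ Φ[(0.10 − 1.96×0.0396)/0.0388] = Φ(0.58) ≈ 72%.

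Simulation of paired tables gives 41 to 42% against 73%. The same steps at ρ=0.3 (changers 0.3253, true standard error 0.0458, McNemar null standard error 0.0466) give 43% against 58%, and simulation agrees. At ρ=0 both tests have about 44%.

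**A second scenario, assumed n=100, change from 50% to 65% (simulated).** At ρ = 0, 0.3, 0.5 and 0.7 the chi-squared test has power 59%, 60%, 62% and 65%. McNemar's test has 57%, 73%, 87% and 99%. The direction is the same: no advantage to the paired test at zero correlation, and a growing one as correlation rises.

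**The case against.** The strongest reply is that the Protocol never writes unpaired, Pearson or independence. McNemar's test is itself a chi-squared-type test, the sentence sits inside an explicit pre/post design, and it ends by allowing further analyses. The authors may have meant the right thing. Part of this stands: the fair statement is that the Protocol does not say the categorical test is paired, not that it expressly chooses an unpaired one. But the same sentence attaches the word to the t-test only, the document's other use of chi-square is between independent arms, and the closing clause adds analyses without replacing the named one. The plain reading remains the ordinary test.

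A chi-squared test could also have a proper use here, for example to compare satisfaction after live and asynchronous sessions attended by different people. That stands, and the fix keeps it.

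Three stronger readings are tempting and are not supported.

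- A reader might infer that the error rate is far below 5% as a matter of fact. That depends on a correlation the Protocol does not give; at zero correlation the rate is nominal. Inflation would need a negative correlation, which is not what one expects when one person answers the same item twice.
- A reader might infer that Aim 1 or the move to UH3 hangs on this test. It does not: the education criterion under UG3 Milestones is that at least 80% of eligible staff complete the module.
- A reader might extend the point to the coalition surveys, where "we will conduct an analysis of variance (ANOVA) based on the portion of the program being evaluated". The Protocol does not say that the same members rate every portion, it does not exclude a repeated-measures ANOVA, and it leaves room for other approaches. That extension is not made here.

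**Conclusion.** The point holds, as a minor one. The Protocol pairs the test for scores and leaves the categorical test unqualified in a design that yields two answers per learner. If the ordinary chi-squared test is used on yes/no items, it is conservative whenever the within-person correlation is positive. Under the assumptions shown, that means a type I error of about 2.8% to 0.6% over correlations of 0.2 to 0.5. With 150 learners and a 10-point rise from 60%, it costs roughly 15 percentage points of power at correlation 0.3 (58 − 43) and a little over 30 at 0.5 (73 less 41 to 42). The learner numbers, proportions and correlations are all assumptions, so these figures show direction and scale rather than predict this study.

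The conclusion also rests on pre and post answers being linked by person. The Protocol does not say so outright, but the paired t-test presupposes it. Only the UG3 education evaluation is affected. The primary outcome, its sample size, its alpha and the randomised comparison are not.

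**What to change.** In the education paragraph under Study Design, Aim 1, replace the chi-squared test with McNemar's test for yes/no items answered before and after a module. State that pre and post answers are linked by person through a study code. Reserve the chi-squared test for comparisons between independent groups of learners.

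The cost is a change of wording. Linkage is already needed for the paired t-test, so no further data are required. If linkage turns out not to be possible, the paired t-test could not be run either, and the whole sentence would have to be reconsidered.
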